## Abstract

**Background:**

Migraine is one of the most frequent headache diseases and impairs patients’ quality of life. Up to now, many randomized studies reported efficacy of prophylactic therapy with medications such as beta-blockers or anti-epileptic drugs. Non-medical treatment, like aerobic endurance training, is considered to be an encouraging alternative in migraine prophylaxis. However, there is still a lack of prospective, high-quality randomized trials. We therefore designed a randomized controlled trial to evaluate the efficacy of aerobic endurance training versus relaxation training in patients with migraine (ARMIG).

**Methods:**

This is a single-center, open-label, prospective, randomized trial. Sixty participants with migraine are randomly allocated to either endurance training or a relaxation group. After baseline headache diary documentation over at least 4 weeks, participants in the exercise group will start moderate aerobic endurance training under a sport therapist’s supervision at least 3 times a week over a 12-week period. The second group will perform Jacobson’s progressive muscle relaxation training guided by a trained relaxation therapist, also at least 3 times a week over a 12-week period. Both study arms will train in groups of up to 10 participants. More frequent individual training is possible. The follow-up period will be 12 weeks after the training period. The general state of health, possible state of anxiety or depression, impairments due to the headache disorder, pain-related disabilities, the headache-specific locus of control, and the motor fitness status are measured with standardized questionnaires.

**Discussion:**

The study design is adequate to generate meaningful results. The trial will be helpful in gaining important data on exercise training for non-medical migraine prophylaxis.

**Trial registration:**

The trial is registered at ClinicalTrials.gov: NCT01407861.

## Background

Migraine is the second most frequent primary headache. With over 10% of people in the German population affected, migraine is a widespread disease leading to high healthcare costs and has a major impact on patients’ quality of life. Prophylactic medication, such as beta-blockers, topiramate, or amitriptyline, is recommended for patients suffering from three or more headache attacks a month [1]. However, medical prophylaxis is not well accepted by many migraine patients due to experienced or anticipated adverse events. Many patients seek non-medical treatment for migraine [2,3]. Endurance training is recommended [4], in particular as part of multidisciplinary treatment programs for migraine treatment [5-7]. Until now there has been insufficient evidence of the efficacy of endurance training due to the lack of randomized trials. Several studies reported a reduction of migraine frequency and intensity with aerobic endurance training. A major shortcoming of these studies is small patient numbers and therefore low statistical power. Aerobic endurance training led to an increased pain threshold in experimentally-induced pain. Most of these trials were conducted during the 1980s. Measurement of plasma beta endorphin levels in only a small number of migraine patients during exercise training cannot replace randomized trials of efficacy [8].

Recently, a Swedish single-center migraine trial comparing exercise training to relaxation training and to medical treatment with topiramate reported data on the efficacy of exercise training for prophylactic migraine treatment [9]. However, randomized trials using different comparators, especially non-pharmacological treatments, are not yet available [10].

We therefore initiated a German single-center trial to study the prophylactic effect of moderate aerobic endurance training versus relaxation training in patients with migraine.

Relaxation training, such as Jacobson’s progressive muscle relaxation, has been investigated in several studies and is effective for migraine prophylaxis [3,11-13].

## Design

This is a single-center, open-label, prospective, randomized study on the prophylactic effect of moderate aerobic endurance training versus relaxation training in patients with migraine.

The procedures and design of the study were approved by the Medical Ethics Committee of the University of Duisburg-Essen in Essen, Germany (Approval number 11–4677) and the study is internationally registered (ClinicalTrials.gov, Registration number NCT01407861).

The study started in July 2011, and participants are recruited via local newspapers, study brochures or local television. Interested participants are informed about the study protocol. After written informed consent, a sport therapist will make an appointment to conduct an endurance test to determine the optimal training heart rate. Participants will be examined by a neurologist to confirm the diagnosis of migraine and to check inclusion and exclusion criteria (see below). Diagnosis of migraine is based on the International Classification of Headache Disorders criteria (ICHD-II) [14].

### Inclusion criteria

Inclusion criteria are as follows:

1. The patient’s signature is on the informed consent document (patients should each be given ample time to read the consent form, ask any questions they may have regarding the trial, and have a clear understanding of the trial and the procedures involved prior to signing the consent form)

2. Patients have a clinical diagnosis of migraine with or without aura according to ICHD-II criteria [14] at least 1 year prior to enrollment

3. Patients have a clinical diagnosis of migraine with or without aura and, in addition, a clinical diagnosis of tension-type headache (TTH) according to ICHD-II [14], if patients are able to differentiate between the two headache diagnoses and if migraine is more frequent in patients with TTH

4. Patients report at least three migraine days per month

### Exclusion criteria

Exclusion criteria are as follows:

1. Diseases or disabilities that disqualify for performing either aerobic endurance training or relaxation training (that is, severe asthma, pacemaker, major depression, specific physical handicap)

2. Language disabilities that disenable filling out questionnaires

3. Fewer than three migraine days per month

4. Pregnancy

5. Additional diagnosis of secondary headache according to the ICHD-II (that is, medication overuse headache)

6. Prophylactic headache medication started within the last 12 weeks

7. Regular performance of endurance training and/or relaxation training at least twice a week

Migraine patients who are stable on prophylactic medication and meet the inclusion and exclusion criteria may be enrolled. Participants will be asked to keep a headache diary during the whole study period. Randomization will be performed at the end of the 4-week baseline period. Each participant will receive a sealed envelope. Randomization sequence is composed by an independent statistician using computer-generated random numbers. Participants are randomized to either the endurance training or the relaxation training group (1:1). Overall, 60 participants are planned to be enrolled in the trial. This is considered as a pilot trial to prove the feasibility of such a trial design and to achieve data on efficacy of both therapies.

The treatment (training) period will begin after baseline headache diary documentation for at least 4 weeks to obtain baseline number of headache days. Training will be in groups of up to 10 participants (Figure 1).

**Figure 1 F1:**
[figure not shown]
Flow chart of study protocol.

### Fitness test

Each participant will perform a Physical Working Capacity Test (PWC) to test the aerobic performance capacity [15,16]. The test will be done using a computer-controlled ergometer with specialized software *Vitality System 6.0* (ERGO-FIT, Pirmasens, Germany). The results, defined as the mathematically-calculated performance at the threshold heart rate, are related to the participant’s body weight and thus converted to an individual value to receive optimal aerobic training heart rate. All test data will be printed out and filed in the participant’s case report form (CRF).

### Intervention: aerobic endurance training

Participants who are enrolled in the exercise group will perform endurance training twice a week for 12 weeks under the supervision of a trained sport therapist. The third training day during the week can be chosen individually. More frequent endurance training is possible. Each training session should be documented in the participant’s training headache and training diary. Endurance training consists of indoor cycling with a warm-up period of 10 min, a 30-min exercise period and a 5-min cool-down phase. Heart rate will be measured during exercise training to acquire optimal aerobic training conditions.

### Active comparison: relaxation training

Participants of the relaxation group (up to 10 people) will receive expert guidance in relaxation training twice a week over 12 weeks. A third training day during the week may also be chosen individually. More frequent relaxation training is again possible and should be documented in the participant’s training headache and training diary. Relaxation training is based upon Jacobson’s Progressive Muscle Relaxation (or PMR), an approved technique for reducing stress and anxiety by alternately tensing and relaxing groups of muscles. Participants will learn a short (about 10 min) and long (about 30 min) version of relaxation training. An audio compact disc containing the relaxation program will be provided to practice relaxation treatment at home.

Consistent participation in either exercise or relaxation is important and will be checked regularly. Up to two absent days in 4 weeks are tolerable.

### Headache and training diary

The headache diary should be kept every day during the trial to collect data about pain intensity, duration, accompanying symptoms, intake of analgesics or triptans, absent days from work/school, and training days for endurance training respectively relaxation training.

### Questionnaires

At baseline, after the 12-week training and 12 weeks after finishing the training period (follow-up), participants will be asked to fill out the following internationally-recognized, standardized questionnaires: the SF-12 (short-form 12), a questionnaire about the general state of health [17]; the HADS-D, a German version of the Hospital Anxiety and Depression Scale to capture possible states of anxiety or depression [18]; the HIT-6 (Headache Impact Test) to measure impairments due to headache disorders [19,20]; the Pain Disability Index (PDI) to measure pain-related disabilities [21]; the HSLC-D, a German version of the Headache-Specific Locus of Control Scale to gather information on the locus of control in headache patients [22]; the FFB-Mot, a self-survey on the motor fitness status consisting of 28 self-report items assessing four basic motor abilities, explicitly cardio-respiratory fitness, strength, flexibility, and coordination [23].

### Primary outcome measure

The primary outcome measure is a reduction of headache days in the last 4 weeks of the 12-week training compared to baseline (4 weeks before the start of training).

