## Trial status

Recruitment of participants started in July 2011 and is expected to end in summer 2012.

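### The primary-outcome baseline is tied to the first training session, not to randomisation, so any delay between the two puts part of it after allocation

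*Protocol article*

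**What the plan says.** The Primary outcome measure section of the protocol article compares headache days in the last 4 weeks of training with a reference period: "compared to baseline (4 weeks before the start of training". This ties the reference period to the first session.

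The text after the list of exclusion criteria gives a second anchor: "Randomization will be performed at the end of the 4-week baseline period". It adds: "The treatment (training) period will begin after baseline headache diary documentation for at least 4 weeks". No maximum is given for the diary phase or for the interval from randomisation to first session. On group size it says: "Training will be in groups of up to 10 participants".

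Three other statements bear on the point:
- Blinding (Design section): "This is a single-center, open-label, prospective, randomized study".
- Disclosure of allocation: "Each participant will receive a sealed envelope". The article does not say when the envelope is opened.
- Source of the outcome (Headache and training diary section): "The headache diary should be kept every day during the trial". Headache days are thus counted by the participants themselves.

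The Statistical analysis section plans means, standard deviations and confidence intervals per arm, and uses them to size a later non-inferiority trial.

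**The concern.** A baseline is protected by randomisation only if it is complete before allocation is known. Here the window is counted back from the first session. If a participant is randomised and then waits, the window moves forward and takes in diary days kept after randomisation.

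In an open-label trial with a self-kept diary, those days can depend on the arm. Expectation could change what is recorded, and a participant could start practising before the first session. The documents do not show that either happens, but the definition leaves room for both. Baseline is subtracted in the primary outcome, so any such effect passes directly into the change score. From there it reaches the per-arm means and SDs that are to inform the phase III sample size.

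**Working it through.** The article gives no figure to reproduce here: there is no stated gap, and the 60 participants are a pilot size without a power calculation. What can be checked is how far the two definitions of baseline drift apart.

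**Step 1. Overlap.** Let g be the weeks from randomisation to first session (not stated; taken here as 0 to 8). The window is the 4 weeks that end at the first session. The share after randomisation is min(g,4)/4.

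| Gap g (weeks) | Share of baseline after randomisation, as written | Share if baseline ends at randomisation |
|---|---|---|
| 0 | 0% | 0% |
| 1 | 25% | 0% |
| 2 | 50% | 0% |
| 3 | 75% | 0% |
| 4 to 8 | 100% | 0% |

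**Step 2. Effect on the change score.** Suppose that knowing the allocation shifts recorded headache days by d per 4 weeks in one arm. Baseline in that arm, and so its mean reduction, moves by d × min(g,4)/4. For d = 1 day this is 0.5 day at g = 2 and 1 day at g = 4 or more. The value of d is hypothetical. If d and g are equal in both arms, the shift cancels in a between-arm difference but stays in each arm's own mean.

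**Step 3. Illustration of possible gaps.** This step rests on assumptions that the article does not state: recruitment lasts 11 to 14 months (my reading of "Recruitment of participants started in July 2011 and is expected to end in summer 2012"), it is evenly spaced, participants are randomised one at a time, and each arm waits to fill a closed group of k. Randomisation is 1:1.

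- Rate per arm: 60/14/2 = 2.14 to 60/11/2 = 2.73 per month.
- Mean gap in weeks: ((k − 1)/2)/rate × 52/12.
- Example, 12 months and k = 5: rate 60/12/2 = 2.5, spacing (52/12)/2.5 = 1.73 weeks, gaps 0, 1.73, 3.47, 5.20 and 6.93, mean 3.5 weeks. The mean overlap is (0 + 0.43 + 0.87 + 1 + 1)/5 = 66%.

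| Group size k | Mean gap (weeks), 11 to 14 months | Mean overlap |
|---|---|---|
| 3 | 1.6 to 2.0 | 40% to 50% |
| 5 | 3.2 to 4.0 | 64% to 70% |
| 10 | 7.2 to 9.1 | 82% to 85% |

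If participants join running groups, or are randomised in a batch when places are ready, g is near 0 and so is the overlap.

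**The case against.** The strongest reply is that the passages describe one window. Read in order, they give a 4-week baseline, then randomisation, then training, so the 4 weeks before training are the 4 weeks that end in randomisation. The open-ended diary phase may only mean that baseline runs longer for some participants and randomisation closes it. The flow chart is not shown and may give the timing. An article can also leave visit windows and envelope handling to the full protocol.

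This reading is available, and it is why no bias can be asserted. It needs a gap of zero, however, and the text does not secure one. The point also does not rest on a missing detail: the article states the window within the primary outcome definition and ties it to an event that follows allocation.

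Three stronger readings are tempting, and the documents do not support them:
- A reader might infer that groups wait to fill, so that most baselines are recorded after randomisation. The article limits group size. It does not say that groups are closed or start together, and two supervised sessions a week would also suit rolling entry.
- A reader might infer that a between-arm comparison or a baseline-adjusted analysis in this trial is compromised. The analysis section plans description per arm in a pilot, so no planned test is affected.
- A reader might want to set the possible shift against the expected precision. The article gives no SD, so that comparison cannot be made from it.

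**Conclusion.** The point holds as a badly fixed definition with a possible bias, not a demonstrated one. The baseline has two anchors that agree only when training starts at once, and the one used for the primary outcome is the one exposed to knowledge of allocation. The exposed share is 0% with no gap, 25% per week of gap, and 100% from 4 weeks on. Which of these applies cannot be told from the article.

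The conclusion assumes that participants learn their arm at or soon after randomisation, which is the natural reading of an open-label design. If the envelope is opened only at the first session, this exposure disappears. The group-filling figures show what could happen under closed groups and are not an estimate for this trial.

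Pilot status limits the harm but does not remove it: the means and SDs are meant to size the next trial, and the Discussion considers a multicentre trial under the same protocol, which would inherit the definition.

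**What to change.** In the Primary outcome measure section, define baseline as the last 28 diary days before randomisation, complete before allocation is disclosed. Use the same definition wherever the baseline period is mentioned. A participant with a longer diary phase contributes the last 28 days before randomisation. Diary days between randomisation and the first session then belong to neither comparison window.

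Report the interval from randomisation to first session by arm, so that readers can see whether there was a wait and whether it differed between the arms.

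The cost is one sentence in the definition and one line in the results. The daily diary already covers the days needed, and the overlap becomes 0% for every gap length, whichever way groups are scheduled.

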### Secondary outcome measures

Secondary outcome measures are as follows: number of headache days 12 weeks after finishing the training (follow-up); consumption of analgesics or triptans; increase in aerobic capability; impact on burden of disease; and the psychological impact of training.

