### Statistical analysis

The aim of this pilot trial is to achieve data on the efficacy of both therapies. The effect of treatment on primary and secondary outcomes will be described by mean, standard deviations and confidence intervals per treatment group. These parameters and a definition of a clinically non-relevant difference will be used for sample size calculation of a randomized phase III trial to show non-inferiority of moderate aerobic endurance training versus relaxation training in patients with migraine [24].

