## Discussion

This is a German single-center trial to study the prophylactic effect of moderate aerobic endurance training versus relaxation training in patients with migraine. We chose two active arms for comparison instead of inactive ‘waiting lists’ as placebo because inactive control groups would bear a high risk of withdrawal from the trial. Furthermore, relaxation training has proven to be effective in migraine treatment [3,11-13] and facilitates comparability, in contrast to medical treatment or ‘just taking a pill’, especially when done in a similar setting to exercise training. The study outcome depends on regular participation in either the exercise or the relaxation training group over a period of 12 weeks. Considering that all of the participants have not performed sports or relaxation training on regular basis before, a relevant drop-out rate cannot be ruled out. In the Swedish trial by Varkey *et al.*, only 85% completed the training, data on about 70% of the participants were collected at follow-up after 3 months, and only 50% of the participants returned questionnaires after 6 months [9]. Compared to the Swedish trial where relaxation training was performed individually, in our trial both exercise and relaxation training will mainly take place in a supervised group to rule out bias due to group dynamics. The overall number of 60 participants (30 in each study arm) may influence the significance of the results. However, Varkey *et al.* used an equal number of participants in their migraine exercise trial. Depending on our results, a multicenter trial with the same protocol may be planned.

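### The follow-up headache-day outcome is a per-arm level with no baseline reference; a baseline-adjusted between-arm difference would be more precise and needs no new data

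*Protocol article*

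**What the plan says.** The protocol article defines the primary outcome with a window at each end and a reference to baseline: "reduction of headache days in the last 4 weeks of the 12-week training compared to baseline (4 weeks before the start of training" (Primary outcome measure).

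The first secondary outcome takes the same diary measure to the end of follow-up, but gives only the "number of headache days 12 weeks after finishing the training (follow-up" (Secondary outcome measures). No baseline is named. The same sentence words aerobic capability as a gain, so change is not assumed throughout the list.

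For the analysis, the effect of treatment on primary and secondary outcomes "will be described by mean, standard deviations and confidence intervals per treatment group" (Statistical analysis). No between-arm difference and no baseline adjustment is named. The stated use of these figures is to size a later non-inferiority trial.

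The data for a baseline-referenced measure are collected in any case. Under Exclusion criteria the article requires "baseline headache diary documentation for at least 4 weeks to obtain baseline number of headache days", and adds: "Participants will be asked to keep a headache diary during the whole study period". The abstract states: "The follow-up period will be 12 weeks after the training period".

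**The concern.** Statistical analysis sets out to describe the effect of treatment. For the primary outcome a per-arm mean does describe a change, because the outcome is itself a change. For the follow-up outcome a per-arm mean of a count is a level. It cannot be set beside the primary result to judge whether a reduction was kept.

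Attrition adds to this. The Discussion expects relevant drop-out. A follow-up mean would come from those still keeping the diary, whereas the baseline mean would come from everyone randomised. A reader who subtracts one from the other compares partly different people.

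The baseline count is usually the obvious covariate for a later count of the same thing. Leaving it out of a between-arm comparison gives up precision in a trial with few participants, at the time point where fewer are likely to remain. The choice of measure also affects which SD is handed on to the later trial: under equal SDs, the SD of a change is sqrt(2(1 − ρ)) times that of the count.

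**Working it through.** The article gives no SD, effect size or power for its sample size, so there is no figure of its own to reproduce. The check is what a between-arm difference at follow-up would look like under three ways of handling baseline.

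**Inputs**
- Randomised: "The overall number of 60 participants (30 in each study arm", from the Discussion, with 1:1 allocation.
- Retention at the 3-month follow-up: about 70% in the earlier Swedish exercise trial, as reported in the Discussion. Applied here as an assumption: 0.70 × 30 = 21 per arm.
- Correlation ρ between baseline and follow-up counts: not given; assumed 0.4 to 0.7.
- SD: not given; results are in SD units, with equal SDs at both times assumed.

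**Formulas** for the 95% half-width of the between-arm difference
- Raw count: t × sqrt(2/n)
- Change from baseline: raw × sqrt(2(1 − ρ))
- Baseline-adjusted count (ANCOVA): raw × sqrt(1 − ρ²)

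**Raw count at n = 21 per arm:** t(0.975, 40 df) = 2.021 and sqrt(2/21) = 0.3086, so 2.021 × 0.3086 = 0.624 SD.

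| Assumed ρ | Raw | Change score | ANCOVA | Equivalent raw n per arm, 21/(1 − ρ²) |
|---|---|---|---|---|
| 0.4 | 0.62 | 0.624 × sqrt(1.2) = 0.68 | 0.624 × sqrt(0.84) = 0.57 | 25 |
| 0.5 | 0.62 | 0.624 × sqrt(1.0) = 0.62 | 0.624 × sqrt(0.75) = 0.54 | 28 |
| 0.6 | 0.62 | 0.624 × sqrt(0.8) = 0.56 | 0.624 × sqrt(0.64) = 0.50 | 33 |
| 0.7 | 0.62 | 0.624 × sqrt(0.6) = 0.48 | 0.624 × sqrt(0.51) = 0.45 | 41 |

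Two things follow.

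1. The change score has a narrower interval than the raw count only when 2(1 − ρ) < 1, that is, when ρ exceeds 0.5. At ρ = 0.4 it is wider (0.68 against 0.62). Copying the primary outcome's change format to follow-up is therefore not enough.
2. The adjusted difference is narrower than both at every ρ in the table. The reduction against the raw count is 1 − sqrt(1 − ρ²): 8%, 13%, 20% and 29%. If ρ were as low as 0.2 the gain would shrink to 2% (sqrt(0.96) = 0.98).

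The percentage gains do not depend on the retention assumption, because n enters all three formulas in the same way.

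**The case against.** The strongest case against is that a condensed article need not give the diary window of a secondary outcome, and that an analysis plan not shown may well adjust for baseline. This stands in part. The missing window alone is not a finding. Nor does the article say that the baseline will be ignored: the diary runs throughout and its use is not excluded. What remains is that the article does state a measure and a method for this outcome, and the stated pair yields a level per arm when a better summary is available from the same data.

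It can also be said that no between-arm follow-up contrast is planned, so the half-widths describe an analysis that the trial does not promise. That is correct. The figures show what adding the contrast with adjustment would give, compared with setting the two arm means side by side.

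Three stronger readings are tempting and are not supported.
- *Chance imbalance biases the follow-up comparison.* "Participants are randomized to either the endurance training or the relaxation training group (1:1", and no stratification by headache days is mentioned. With 30 per arm the baseline difference has a standard error of sqrt(2/30) = 0.258 SD, so a gap above 0.3 SD in either direction has a probability of about 25%. But this is random error that the standard error of the raw difference already covers. It reaches follow-up only by the factor ρ, and a change score carries it with the opposite sign by the factor 1 − ρ.
- *This is the trial's only evidence on persistence.* The Questionnaires section repeats six instruments at the same follow-up point. It is the only headache-day outcome after training, not the only evidence.
- *The outcome could be a total over all 12 weeks.* The Questionnaires section uses nearly the same phrase for an assessment time point, so that reading is strained.

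**Conclusion.** The point holds as an available improvement in method, not as an error that invalidates the trial. As written, follow-up headache days are reported as a level among those still followed, off the primary outcome's scale and with no stated use of the baseline diary.

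Adding a baseline-adjusted difference would narrow the between-arm 95% half-width from 0.62 SD to between 0.57 and 0.45 SD. This rests on an assumed 21 per arm, an assumed ρ of 0.4 to 0.7 and equal SDs. The retention figure comes from another trial, whose relaxation arm trained individually, and the documents give neither SD nor ρ. The gain is in precision, and adjustment should not be presented as removing bias. Importance is modest, because this is a secondary outcome in a pilot whose stated analysis is descriptive.

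**What to change.** 1. In Secondary outcome measures, define the outcome as headache days in the last 4 weeks of the 12-week follow-up, to match the primary outcome's window.
2. In Statistical analysis, keep the per-arm description and add, for this outcome, a between-arm difference with its 95% confidence interval from an ANCOVA adjusted for the 4-week baseline count.
3. Report per-arm change from baseline as description only, computed in participants with diary data at both times, with the number contributing. It should not replace the adjusted difference, since it is more precise than the raw count only if ρ exceeds 0.5.
4. Report the observed SD and ρ, so that the later trial can be sized on the measure it will use.

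The cost is a sentence or two of text and one extra model. No new data are needed, because the diary is already kept from baseline to the end of follow-up.
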